**Time of study duration:**
Approximately 2 years.

### Subjects

In total, 150 women suffering from moderate to severe PMS will be randomly allocated to one of the three study groups.

### Patient and public involvement statement

Previous studies about patient experiences in OLP and placebo trials of irritable bowel syndrome were consulted for this study to include patient experiences.^15^

### Patient eligibility

Women aged between 18 and 45 years with a regular menstrual cycle, suffering from moderate to severe PMS reported by prospective self-report are eligible for study participation.^16^ A moderate to severe PMS diagnosis and the primary outcomes are identically assessed and calculated (for more details, see the Primary outcome measures section). Moreover, women have to be capable of consent, fluent in German and have a menstrual cycle duration ranging from 24 to 31 days. The severity of PMS must warrant the treatment of at least one functionally impairing physical or psychological symptom based on the women’s self-report.^10^ Also, participants have to know a general practitioner or gynaecologist who they would consult if necessary. The recent initiation of a new medication (ie, within the last 30 days) leads to study exclusion or delayed enrolment, whereas the intake of any psychopharmacological or psychotropic substance or alcohol abuse lead to exclusion. Further exclusion criteria are pregnancy, breast feeding, indications of a psychiatric or gynaecological disorder, suicidality, further drug intake affecting PMS symptoms, a body mass index above 30, hypersensitivity or allergy to the placebo pills, participation in another study with drugs or in another PMS study within the last 3 months and participation in psychotherapy due to PMS.

### Recruitment

Participants are recruited via advertisement for ‘a novel efficacy study of an integrative and side-effect free intervention against premenstrual complaints’ with flyers and posters at ambulant gynaecologists in the Region of Basel and in the gynaecological clinic of the University Hospital of Basel. Moreover, different internet platforms are used for advertisement and different public facilities and stores around Basel, including the German border region.

Potential participants are informed that participation in the study is voluntary, withdrawal of consent is possible at any time without mentioning reasons, and refusal of study participation will not lead to any negative consequences. Interested women obtain a study information form (online supplementary materials 1 and 2) and all relevant information are also provided during the informed consent process with the opportunity to clarify questions. Women are only enrolled after written informed consent obtainment.

10.1136/bmjopen-2019-032868.supp1Supplementary data

### Trial treatment and study arms

Following recruitment and verification of study eligibility - including a prospective PMS screening for one menstrual cycle - qualified women are allocated randomly by means of a random allocation sequence using the built-in random number generator in Microsoft Excel to one of the three study groups at the study visit (t0) and also are informed before any intervention, respectively the control contact starts: (1) a TAU group, (2) an OLP+ group and (3) an OLP− group (see also figure 2).

**Figure 2 F2:**
[figure not shown]
Overview of study groups. OLP, open-label placebo; TAU, treatment as usual.

The TAU group serves as a control group and has the same amount of contacts with the study team. However, participants of this group do not receive any intervention nor any information concerning the intervention. However, they are told why the control group is valuable and essential for the trial and that they will receive the intervention after study conclusion if desired. They are allowed to continue any medication intake, if the substance does not lead to study exclusion and PMS complaints are still prevalent. The same is warrant for both intervention groups.The OLP+ group obtains the intervention with a plausible treatment rationale. The intervention is provided at the personal meeting at the study site (t0), followed by a second study contact after 3 weeks by phone or if desired by participants again at the study site (t1) and a last post-treatment phone contact and assessment after the second treatment cycle (t2). The intervention consists of an administration of OLP pills including the instruction to take two pills a day for 6 weeks. The pill intake in both OLP intervention groups starts at the very day after the study visit (t0). The study visit (t0) occurs during the first 14 days of the menstrual cycle of each participant, that is, in the follicular phase. Due to the cyclicity of PMS symptoms, we decided to provide the intervention for a longer period of time in contrast to previous OLP studies^1–3^ to encompass at least one whole menstrual cycle. After the explicit mentioning of the pharmacological inertness of the pills in both groups, the OLP+ group receives—in contrast to the OLP− group—additionally a comprehensive OLP treatment rationale (see online supplementary material 3) at t0 as well as at t1. The discussion points encompass: (a) that placebos can be powerful, also for PMS, (b) an explanation on why placebos work, (c) that faithful pill intake is crucial and that doubts do not have a negative effect on the treatment, (d) that placebos have also been shown to work without deception. Moreover, a video sequence of about 2 min is shown of an American NBC news report with German subtitle about an OLP intervention on irritable bowel syndrome including a patient report (see https://www.youtube.com/watch?v=uv0SuWKZjsI&t=1s). Neither participants nor study team members are blinded. Yet besides the treatment provider, study team members are not informed about group allocation to minimise investigator bias. As investigational product, pink oral placebo pills—‘P-Dragees rosa Lichtenstein’ of the German brand *Winthrop—*are administered which are certified placebo pills without any active ingredient and with validated quality. Each pill contains the following substances: lactose monohydrate; magnesium stearate (Ph. Eur.); microcrystalline cellulose; highly dispersed silicon dioxide; white clay, magrogol glycerolhydroxy stearate (Ph. Eur.); Arabic gum; montanglycol wax; povidone (K 25); talcum; titanium dioxide (E 171); erythrosine; aluminium salt (E 127); calcium carbonate; sucrose; glucose syrup; maize starch; macrogol 6000. Also, participants of both intervention groups receive a certificate, confirming that the study medication only contains placebo pills.The OLP− group obtains the same intervention and intake instruction like the OLP+ group and the proceeding is identically. However, no treatment rationale or further treatment explanation is provided.

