## Rationale

PMS entails clinically significant somatic and psychological symptoms in the premenstrual phase of the menstrual cycle, causing substantial distress and functional impairment.^10^ Worldwide, a considerable amount of women of reproductive age are affected with a pooled prevalence of 47.8%.^11^ Subsequently, a myriad of distinctive therapies are prescribed for PMS—including pharmacological and phytopharmaceutic drugs as well as complementary interventions^12^—yet there is limited evidence for some interventions (eg, Chaste tree; anxiolytics) while other empirically validated interventions (eg, selective serotonin reuptake inhibitors, hormonal therapy) show considerable side-effects.^13^

Notably, PMS seems to be highly susceptible to placebo effects: The Royal College of Obstetricians and Gynaecologists alerts to substantial placebo responses in randomised-controlled PMS intervention trials of 36%–43%^7^ and different studies reported considerable placebo effects on PMS.^8 9 14^ Furthermore, PMS offers the opportunity to investigate OLP effects on *both* somatic and psychological symptoms since symptom diaries like the German PMS symptom diary inquire about physical (eg, breast tenderness, headaches, joint and muscle pain) as well as psychological symptoms (eg, depressed mood, hopelessness, irritability). In addition, we are the first to assess the effect of a comprehensive OLP treatment rationale in a clinical population. We hypothesise that first, women obtaining an OLP treatment with a treatment rationale will report less PMS symptom intensity and interference during the course of the intervention and at follow-up, compared to women obtaining an OLP treatment without a treatment rationale. Second, we assume that women receiving an OLP treatment without a treatment rationale will also show a higher decrease in PMS symptom intensity and interference in comparison to the treatment as usual (TAU) group which is not given any of the treatment-specific information that the OLP groups receive nor the rationale for the OLP treatment.

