**Figure 1 F1:**
[figure not shown]
Study design and flow of participants*.* IC, informed consent; OLP, open-label placebo; PMS, premenstrual syndrome; TAU, treatment as usual.

**Table 1 T1:** Study schedule

Study periods	Screening phase			Intervention phase				
	Preliminary screening of eligibility	Prospective PMS screening	L1 OA	Personal meeting (t0)	L2 OA	Midpoint study contact	L3 OA	Post-treatment study contact & OA (t2)
Visit/contact	Phone/post/online	At home (diary form)	Online	At study site	Online	At study site or phone/Skype	Online	Phone +post-treatment online
Day of menstrual cycle (MC)	−31–−1 day of 1. MC	1. day of 1. MC until end of 1. MC	−5–−1 of 2. MC	1–14 day of 2. MC	−5–−1 of 3. MC	1–14 day of 3. MC	−5–−1 of 4. MC	1–14 day of 4. MC
Menstrual phase	At any point	One whole MC	Luteal	Follicular	Luteal	Follicular	Luteal	Follicular
Time (min)	20	2 daily for 1 MC	10	60	10	15	10	30
Study information/informed consent	x							
Inclusion/exclusion criteria	x	x		x				
Randomisation				x				
Placebo dragée intake in intervention arms				x	x	x	x	
Narrative for OLP+ group				x		x		

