## Outcome measures: primary, secondary and tertiary

### Primary outcome measures

The German PMS symptom diary consists of 27 symptoms and of three further items assessing interference in different domains (ie, work or school; social activities; relations with others). Usually, a four point Likert scale is employed, however, in line with Endicott *et al*
17 we apply a six point Likert scale to be able to detect subtle changes. We compare changes over time of PMS symptom intensity and interference across three menstrual cycles. The *PMS symptom intensity score* is derived from the first 27 items of the German PMS symptom diary, and the *symptom interference score* is derived from the last three items. With regard to symptom intensity, two additional subscales are calculated by dividing the 27 symptom items into a psychological symptom intensity subscale and a physical symptom intensity subscale score (see secondary outcomes).^17^

Following Kues *et al*
18 and Janda *et al*,^16^ we calculate separate scores for the luteal and follicular phase and consider the difference for our analysis. In more detail, we conservatively consider 7 days prior to menstruation onset as a time slot for the luteal phase and 7 days of the follicular phase, whereas the start of the follicular phase for each participant is calculated using the following formula: (individual cycle duration in days−14)/2=first day of the follicular phase. Subsequently, we calculate the difference score of the means for each menstrual cycle for the respective primary outcome of interest (ie, for PMS symptom intensity or interference). Intensity and interference are considered as marked if rated by participants with at least a 4 (very strong) on a scale from 0 (not at all) to 5 (extreme). Moreover, the item has to be rated with at least a four for at least two consecutive days to be considered as marked. Further, symptoms only are considered as marked symptoms if the respective symptom is not marked in the follicular phase and if it is associated with marked interference in the luteal phase. If a participant has four or more symptoms marked in the luteal phase, also interference of only 1 day is accepted. We are also interested in the trajectory of the symptoms in the intervention groups across the two luteal phases after t0. Hence, we will compare if there are differences of group effects at cycle 2 (C2) and cycle 3 (C3) in contrast to cycle 1 (C1).

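### The fixed 6-week course often ends before or during the C3 luteal outcome window, although the schedule presents C3 as a treated cycle; a C2-to-C3 change in group effect is then mixed with stopping the pills

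*Protocol article*

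**What the plan says.** All references are to the protocol article.

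- **Dosing** (Trial treatment and study arms): the course is given "including the instruction to take two pills a day for 6 weeks". Intake "starts at the very day after the study visit (t0"), and that visit "occurs during the first 14 days of the menstrual cycle of each participant". Table 1 identifies this as cycle 2. The reason given for the duration is "to encompass at least one whole menstrual cycle".
- **Cycle length** (Patient eligibility): women must "have a menstrual cycle duration ranging from 24 to 31 days".
- **Outcome window** (Primary outcome measures): the luteal score uses "7 days prior to menstruation onset as a time slot for the luteal phase". The same section plans to look at the symptom trajectory over the two luteal phases that follow t0, and to compare group effects at C2 and C3 with C1.
- **Primary model** (Statistical analysis): cycle has three levels (C1, C2, C3), and the interaction of group contrast and cycle is the term of main interest.
- **Schedule** (Table 1): the row for placebo "intake in intervention arms" carries marks at t0, L2, the midpoint contact and L3. L3 is the online assessment in the five days before cycle 4.
- **Labels elsewhere**: the sections on the PMS-Impact Questionnaire, the SF-12 and the relationship satisfaction scale all place L2 and L3 in the intervention phase. The treatment section dates t2 to the end of a second treatment cycle.

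**The concern.** The dosing rule is fixed in calendar days, while the outcome windows are fixed by menstruation. A 42-day course that starts somewhere in the first half of cycle 2 need not reach the end of cycle 3, yet the schedule and the surrounding text treat C3 as a treated cycle.

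C3 is one of only two post-baseline points in the primary interaction. If the C2 luteal score is always obtained on pills and the C3 luteal score often partly or wholly after the last pill, a group effect that shrinks or grows between the two has at least two readings: a change in response during treatment, or the consequence of stopping. The TAU arm removes natural time trends but not this, and the described model has no term for it. A reader who trusts Table 1 would take the C2-to-C3 trajectory as change on treatment.

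**Working it through.** **Inputs.** Course 42 days; visit day d = 1 to 14 of cycle 2; cycle length L = 24 to 31 days; luteal window 7 days; L3 window 5 days. Days are counted from day 1 of cycle 2, with cycles 2 and 3 both of length L.

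**Formulas.**
- Pill days: d+1 to d+42.
- C2 luteal window: L-6 to L. C3 luteal window: 2L-6 to 2L. L3 days: 2L-4 to 2L.
- C3 luteal window fully covered if d+42 ≥ 2L; wholly uncovered if d+42 < 2L-6.

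**The plan's own aim.** The longest permitted cycle is 31 days, and 42 ≥ 31, so the course does encompass at least one whole cycle for every permitted L.

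**One case by hand.** With L = 28, cycle 3 ends on day 56 and its luteal window opens on day 50. A visit on day 7 puts the last pill on day 49, so the window has no pill day. Full coverage needs d+42 ≥ 56, that is, a visit on day 14.

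**All 8 × 14 = 112 combinations, C3 luteal window** (number of the 14 visit days):

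| L | Full | Part | None |
|---|---|---|---|
| 24 | 9 | 5 | 0 |
| 25 | 7 | 6 | 1 |
| 26 | 5 | 6 | 3 |
| 27 | 3 | 6 | 5 |
| 28 | 1 | 6 | 7 |
| 29 | 0 | 5 | 9 |
| 30 | 0 | 3 | 11 |
| 31 | 0 | 1 | 13 |
| Total | 25 (22%) | 38 (34%) | 49 (44%) |

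So 38 + 49 = 87 of 112 (78%) are not fully covered. The mean coverage is 2.7 of 7 days.

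**Related counts.**
- C2 luteal window: fully covered in 112 of 112.
- L3 days: no pill day in 63 of 112 (56%); at least one in 49.
- The shortest intake within cycle 3 is d+42-L = 1+42-31 = 12 days, so every combination has some treated days in C3.
- The last pill precedes the last day of C3 by at most 2L-(d+42) = 62-43 = 19 days.

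**Sensitivity to the assumptions.**

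| Variant | Not fully covered | Wholly uncovered |
|---|---|---|
| Visit days 1-7 | 54 of 56 (96%) | 37 of 56 (66%) |
| Visit days 8-14 | 33 of 56 (59%) | 12 of 56 (21%) |
| Visit days 11-14 | 16 of 32 (50%) | 4 of 32 (12.5%) |
| Visit day 14 only | 3 of 8 | 0 of 8 |
| C2 and C3 lengths vary independently over 24-31 | 733 of 896 (82%) | 385 of 896 (43%) |

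**Course needed to reach the end of the C3 window:** 2L-d days, from 48-14 = 34 to 62-1 = 61; for a 28-day cycle, 42 to 55.

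**The case against.** **The duration was a deliberate choice and its aim is met.** This stands: six weeks was justified only as covering one whole cycle, and it does. That aim does not reconcile the course with the L3 intake mark or with the description of C3 as treated.

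**Off-pill observation is compatible with the plan**, since the hypothesis expects an effect "during the course of the intervention and at follow-up". This is true of the hypothesis, but the document does not leave C3 unlabelled: it places L3 in the intervention phase. It can be replied that Table 1 also lists the post-treatment contact under that heading, so the heading may only name a schedule period. That weakens the heading as evidence. It does not explain the intake mark at L3 or the reference to a second treatment cycle.

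**The L3 mark is not false for everyone.** Correct: 49 of 112 combinations have at least one pill day among the L3 days. The column position is also read from an extracted table, although the text labels support it.

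**The shares depend on equal weights.** This stands. The document gives no distribution of visit day or cycle length. If visits cluster late in the window, the problem shrinks, and with visits on days 11-14 half the combinations are fully covered.

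**Is C3 unusual in mixing on-pill and off-pill days within the luteal-minus-follicular score?** A reader might infer so, because the C3 follicular window is almost always on pills. The plan's definitions do not support treating this as a C3 fault. By the follicular formula, the C2 follicular window is fully on pills in only 44 to 48 of 112 combinations and wholly before the first pill in 16 to 20, depending on rounding. Both post-baseline scores can be mixed.

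**Conclusion.** The point holds as an inconsistency between the dosing rule and the schedule, with a limited consequence for interpretation. Under equal weights, the C3 luteal window is not fully covered in 87 of 112 permitted combinations and not covered at all in 49. For visits on days 8-14 the figures are 33 and 12 of 56. These counts assume intake exactly as instructed and say nothing direct about the proportion of women.

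Three stronger readings are tempting and are not supported:
- **That the randomised comparisons are biased.** They remain valid as effects of assignment to a 6-week course, and the two placebo arms follow the same dosing rule.
- **That the C3 effect is diluted by a known amount.** This depends on how quickly a response fades after stopping, for which the document gives no figure.
- **That on-treatment change and stopping can never be told apart.** The scheduled stop day follows from the t0 date, so coverage can be examined. They are mixed in the analysis as planned.

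What remains is that a C2-to-C3 change in group effect should not be read as a trajectory on treatment.

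**What to change.** 1. Correct the intake mark at L3 in Table 1, the intervention-phase wording for L3 in the three questionnaire sections, and the reference to a second treatment cycle in the treatment section.
2. State that the C3 luteal score is often obtained partly or wholly after the last pill, and do not interpret the C2-to-C3 trajectory as change on treatment.
3. Keep the primary model. Add one descriptive sensitivity analysis of the C3 group effect by scheduled share of the C3 luteal window on pills. Compute the share in all three arms from the t0 date and the C1 cycle length, both known at randomisation, and include C1 length as a covariate.

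The cost is wording plus one analysis of dates already collected; dosing, visits and sample size do not change. The analysis has limits: coverage is not randomised, and C1 length is an imperfect proxy for later cycles. If C2 and C3 each lie within 2 days of C1 and within 24-31 days, the proxy misclassifies full, part or none in about 19% of equally weighted combinations. If the three lengths are independent over 24-31 days, it does so in about 50%.

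Only if two treated luteal phases were intended, instruct intake until the onset of cycle 4. That means 34 to 61 days, or 68 to 122 pills instead of 84. As enrolment began in August 2018, a change during the trial would mix two dosing rules.

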
### Detailed screening and PMS assessment

After informed consent obtainment, participants are comprehensively screened for study eligibility. Therefore, the following information is collected online:

Verification of eligibility according to eligibility criteria.Medical and gynaecological history.Assessment of sociodemographic data.Assessment of PMS retrospectively.

In a second step, women fulfilling eligibility criteria and PMS criteria retrospectively, start a prospective PMS screening with daily online surveys as part of a PMS symptom diary assessment for one menstrual cycle for the screening and in total for three menstrual cycle for primary outcome assessment (see below).

## Outcome measures: primary, secondary and tertiary

### Primary outcome measures

The German PMS symptom diary consists of 27 symptoms and of three further items assessing interference in different domains (ie, work or school; social activities; relations with others). Usually, a four point Likert scale is employed, however, in line with Endicott *et al*
17 we apply a six point Likert scale to be able to detect subtle changes. We compare changes over time of PMS symptom intensity and interference across three menstrual cycles. The *PMS symptom intensity score* is derived from the first 27 items of the German PMS symptom diary, and the *symptom interference score* is derived from the last three items. With regard to symptom intensity, two additional subscales are calculated by dividing the 27 symptom items into a psychological symptom intensity subscale and a physical symptom intensity subscale score (see secondary outcomes).^17^

Following Kues *et al*
18 and Janda *et al*,^16^ we calculate separate scores for the luteal and follicular phase and consider the difference for our analysis. In more detail, we conservatively consider 7 days prior to menstruation onset as a time slot for the luteal phase and 7 days of the follicular phase, whereas the start of the follicular phase for each participant is calculated using the following formula: (individual cycle duration in days−14)/2=first day of the follicular phase. Subsequently, we calculate the difference score of the means for each menstrual cycle for the respective primary outcome of interest (ie, for PMS symptom intensity or interference). Intensity and interference are considered as marked if rated by participants with at least a 4 (very strong) on a scale from 0 (not at all) to 5 (extreme). Moreover, the item has to be rated with at least a four for at least two consecutive days to be considered as marked. Further, symptoms only are considered as marked symptoms if the respective symptom is not marked in the follicular phase and if it is associated with marked interference in the luteal phase. If a participant has four or more symptoms marked in the luteal phase, also interference of only 1 day is accepted. We are also interested in the trajectory of the symptoms in the intervention groups across the two luteal phases after t0. Hence, we will compare if there are differences of group effects at cycle 2 (C2) and cycle 3 (C3) in contrast to cycle 1 (C1).

Moreover, we evaluate the effect of a comprehensive OLP treatment rationale, by providing one intervention group with a comprehensive treatment rationale in addition to intake instructions whereas the other intervention group only obtains intake instructions (see also the Trial treatment and study arms section).

